#### Willingness of clinicians to recruit participants

The numbers of patients identified, screened and randomised will be evaluated by study site. Differences between sites will be considered and potential differences, such as the willingness of clinical staff to refer patients, considered.

#### Analysis of secondary outcome

##### Effect of tDCS

To evaluate the effect of tDCS on OCD symptoms, Y-BOCS scores at all time points in the 3 treatment conditions (Sham, OFC, SMA) will be estimated. Comparison of the OFC and SMA targets will be considered using paired tests to determine if one target is superior to the other. As the sample size is small, it is not expected that this study will have the power to evaluate with certainty the superiority of either target, but may provide an indication for one stimulation target over the other.

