### Design

This feasibility study is designed as a double-blinded, sham-controlled, crossover randomised multicentre design in adults with OCD.

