### Randomisation scheme

Patients enrolled will be randomised to one of six permutations (4 per group):A—Sham: SMA: OFCB—Sham: OFC: SMAC—SMA: OFC: ShamD—SMA: Sham: OFCE—OFC: Sham: SMAF—OFC: SMA: Sham

The participant will sign the consent to study enrolment and randomisation. The clinician will have authorised access to the online randomisation programme. They will be provided with an identification code and password to access the randomisation programme. The clinician will enter the specific internet site, using their username and password and enter the study Patient Identification Number (PID), which includes the centre code. The computer will allocate the next consecutive randomisation allocation recorded automatically on the CRF. The clinician will record which intervention the patient was randomised to in the patients’ medical records and in a sealed envelope into the trial master file (TMF).

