### Stimulation schedules

The stimulation protocol in FEATSOCS has been designed according to expert recommendations regarding the safety of tDCS, developed for research ethics committees and Institutional Review Boards, as well as in clinical practice [43]. The application of tDCS has presented minimal risk in numerous research or clinical studies when applied within standard parameters. Minimal risk means there have been no serious adverse events, that common adverse effects such as reddening of the skin are mild and short-lived, and that reasonable efforts at assessment have determined there is no evidence of brain damage. Standard parameters to date mean that (1) the current is less than 2.5 mA, (2) it is applied through electrodes that are known to minimize skin burns at the specific current level, (3) the current application duration is less than 20–60 min per session, and (4) sessions are not more frequent than twice per day [42, 43]. In line with these recommendations, each participant will receive two 20-min stimulations separated by 4 h on Day 1 and on Day 2 of each session comprising:Cathodal tDCS 2 mA to the bilateral SMACathodal tDCS 2 mA to the left OFCSham tDCS to the OFC or SMA

The courses will be allocated in a randomised and counterbalanced order. Each 2-day course of tDCS will be spaced 4 weeks apart to avoid carry-over effects, and allow for the duration of effect to be evaluated. Patients will be assessed before each stimulation, up to 4 h afterward, with the assessments at 4 h after the second stimulation may be conducted over the phone, and then at 24 h and 7,14 and 28 days following tDCS stimulation.

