### Sample size calculation

Study sample size is evaluated with respect to the primary outcome (difference in the challenge Y-BOCS between tDCS and Sham), given that the aim is to estimate the likely effect size of a future trial. We assume that the sample will be representative of the population, and that the observed variance, and Y-BOCS scores in each condition will allow for estimation of a typical group comparison. Given that there are only 4 exposures of tDCS in each study condition, with 4 weeks between exposures, we assume no carry-over effects, which will be tested using a mixed model. Each tDCS target (OFC and SMA) will be considered independently against Sham. Published estimates of effect size vary widely [45]; thus, a conservative estimate of *d* = .3 is assumed. Following Cocks and Torgersen [51], assuming *α* = 0.05, 1 – *β* = 0.80, a sample size of 20 per group allows detection of a lower limit of *d*’ > 0.1 for an expected effect size *d*’ = 0.3. An additional 5 patients will allow for a 25% dropout.

It is estimated that approximately 25 patients will be recruited from a pool of 200 patients identified from screening, giving power to estimate the ascertainment ratio to within ± 6%. The proportion of missed treatment sessions is expected to be less than 20% from a total of 206 sessions, giving a precision within ± 6%. At the outset of the study, it is not possible to estimate the likely number of reported adverse events (safety), which is expected to be low, and cannot therefore estimate the likely precision of estimation.

Time-dependent changes in the Y-BOCS scores, and in the CANTAB test scores will be considered using standard paired comparisons (*t* test). A sample size of *N* = 20 allows for detection of an effect size *d*’ = .65 with power 1 – *β* = .78, and an effect size *d*’ = .77 with power 1 – *β* = .90. A time-dependent model will be evaluated (mixed model) to examine trends over time, but with limited power.

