##### Likely effect size

The primary focus on comparisons will be on the potential effect size at 24 h after the final stimulation in each treatment condition. The observed and the lower limit for the effect size for the OFC and SMA targets will be evaluated with respect to the Sham condition, assuming that no carryover effects are observed in the crossover design (mixed model). A lower limit for effect size of < 0.1 will indicate a positive signal to proceed. Where possible, treatment target differences will be adjusted in a mixed model to account for baseline values of key patient variables.

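### The OFC v SMA comparison is fixed as a paired test with no term for course order, although the trial balances its six sequences on order: adding period is a free gain in precision

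*Protocol article*

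**What the plan says.** Under Randomisation scheme, the article lists all six orders of the three conditions, with four patients per order. Under Stimulation schedules it adds: "The courses will be allocated in a randomised and counterbalanced order".

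Under Effect of tDCS, the comparison of the two active targets is fixed: "Comparison of the OFC and SMA targets will be considered using paired tests to determine if one target is superior to the other".

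Under Likely effect size, the contrasts of each target with sham are tied to a mixed model, and the adjustment named is: "Where possible, treatment target differences will be adjusted in a mixed model to account for baseline values of key patient variables".

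The only order-related effect the article addresses is carry-over. Under Sample size calculation: "we assume no carry-over effects, which will be tested using a mixed model". Course number, period or sequence is not named as a term in any comparison.

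**The concern.** A crossover that uses all six orders is balanced so that a general shift from course 1 to course 3 does not favour any condition. Such a shift could come from regression towards the mean after entry at Y-BOCS 20 or more, from expectation, or from medication that need have been stable for only 6 weeks. Balance keeps the shift out of the mean difference but not out of its variance: a paired test leaves it in the error term. A paired test also discards every patient who has only one of the two courses being compared.

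The adjustments the article does name do not deal with this. A fixed patient characteristic is the same in all three courses and cancels within the patient. A test for carry-over asks whether one condition affects the next course, which is a different question from whether all patients drift.

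At stake is the precision of the comparison meant to indicate the better target. If dropout leaves the orders unbalanced, some bias in that comparison is also possible.

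**Working it through.** **The plan's own figures.** The article's paired-test power figures (Sample size calculation, N = 20) reproduce. A two-sided paired t test at α = 0.05 gives power 0.787 at d' = 0.65 (stated 0.78) and 0.904 at d' = 0.77 (stated 0.90). They are stated for changes over time and are not in question here. The article gives no drift between courses, so there is no planned figure for that to reproduce.

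**Course positions, OFC minus SMA, from the six listed orders.**

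| Order | OFC course | SMA course | Difference |
|---|---|---|---|
| A | 3 | 2 | +1 |
| B | 2 | 3 | −1 |
| C | 2 | 1 | +1 |
| D | 3 | 1 | +2 |
| E | 1 | 3 | −2 |
| F | 1 | 2 | −1 |

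The mean is 0 and the mean square is (1+1+1+4+4+1)/6 = 2. The same mean and mean square hold for OFC v sham and SMA v sham. A linear drift of t points per course therefore cancels from the balanced mean and adds 2t² to the variance of the paired difference.

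**Effect on the SD.** Assume a within-course SD of 4 points (not in the article). The paired-difference variance without drift is 2 × 16 = 32, so the SD is multiplied by √(1 + 2t²/32):
- t = 1: √(34/32) = 1.031
- t = 1.5: √(36.5/32) = 1.068
- t = 3: √(50/32) = 1.250

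**Simulated 95% CI widths.** Settings: 25 patients over the six orders, 5 stopping after course 1 or 2, SD 4. The paired t interval is set against a within-patient model with period that uses all available courses. The contrast simulated was target v sham. Because the position differences have the same mean square for every pair, the widths carry over to OFC v SMA.

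| Drift per course | Paired | With period | Narrower by |
|---|---|---|---|
| 0 | 5.13 | 4.96 | 3% |
| 1 | 5.28 | 4.97 | 6% |
| 1.5 | 5.46 | 4.96 | 9% |
| 3 | 6.42 | 4.97 | 23% |

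The closed form agrees: 5.13 × 1.031 = 5.29, 5.13 × 1.068 = 5.48 and 5.13 × 1.250 = 6.41. At 1 point, about half of the gain (5.13 to 4.96) comes from using incomplete patients and from extra degrees of freedom. The other half (5.28 to 5.13, 3%) is the drift itself.

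**Which row is plausible.** The only anchor is in the Background: the sham arm of a cited trial changed by 2.84 points by week 12. Spread evenly over three 4-week courses, that is 2.84/3 = 0.95 points per course. A separate simulation at 0.95 gave 5.25 v 4.95, again about 6%.

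**Bias.** A paired estimate is shifted by drift × mean position difference among the patients analysed.
- Four per order: 0.
- Order F lost entirely (20 left): OFC v SMA 4 × (1−1+1+2−2)/20 = 0.2, so 0.2 points at a drift of 1.
- Orders D and E each halved (also 20 left): (4−4+4+4−4−4)/20 = 0, no bias.
- Random loss of 5 from 25: the mean difference has SD 0.155. This is chance imbalance, not systematic bias.
- Sham-first patients three times as likely to stop (assumed): SMA and sham differ by 0.13 of a course on average, giving 0.13 to 0.4 points for drifts of 1 to 3.

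In the lost-sequence case the period-adjusted estimate showed bias of about 0.

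**The case against.** The strongest reply is that this is a feasibility study. Its primary analysis is descriptive, and the article says it does not expect power to settle which target is superior. In a balanced design the paired estimate is unbiased and its interval errs wide. That stands: the paired standard error does not make the test invalid. It costs precision.

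A reader might infer that the effect-size lower limit used for progression is too low. The article does not support that. The limit belongs to the contrasts with sham, for which Likely effect size names a mixed model and no paired test. The terms of that model may be completed in an analysis plan not shown. What can be said is that the one adjustment the article names there would not remove a drift.

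A reader might also extend the point to every paired test in the article. The tests of change over time (Sample size calculation, Duration of effect) are naturally read as comparisons within one course, where a shift between courses cancels. They are not affected.

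Size is open to challenge too. The SD and the drifts are assumptions, and the anchor is on the standard Y-BOCS, whereas the sample-size section names the challenge version. Each course has its own baseline, so if the comparison used change from that baseline, a pure level shift would cancel. A response that changes in size over courses would remain, and the section on Effect of tDCS refers to scores, not changes. These points argue for the small end of the range. They do not argue against naming period.

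**Conclusion.** The point holds as a free improvement. The article fixes paired tests for OFC v SMA and names no period term, although the trial balances conditions over courses. With SD 4 and 5 of 25 lost, the 95% CI would be about 3% narrower with no drift and about 6% narrower at roughly 1 point per course, the order the cited sham arm suggests. A gain of 23% needs 3 points per course, or 6 points from course 1 to course 3, and should be read as an extreme.

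Dropout alone does not bias the paired estimate, though a reader might take it to. Bias needs a drift and also losses that leave the orders unbalanced on course position. Even in the assumed sham-first scenario, 0.13 to 0.4 points is small beside a CI half-width of about 2.6 to 3.2. In every drift setting run, the model with period gave the narrower interval.

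**What to change.** Under Effect of tDCS, replace the paired test for OFC v SMA by a mixed model with condition and period (course 1, 2, 3) as fixed effects and patient as a random effect, using every completed course.

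Under Likely effect size, include period in the mixed model that gives OFC v sham, SMA v sham and the effect-size limit. Paired differences can stay as a descriptive summary. The within-course time comparisons need no change.

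The cost is 2 degrees of freedom out of about 40 and a change of wording. No extra patients, visits or data are needed.

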##### Likely effect size

The primary focus on comparisons will be on the potential effect size at 24 h after the final stimulation in each treatment condition. The observed and the lower limit for the effect size for the OFC and SMA targets will be evaluated with respect to the Sham condition, assuming that no carryover effects are observed in the crossover design (mixed model). A lower limit for effect size of < 0.1 will indicate a positive signal to proceed. Where possible, treatment target differences will be adjusted in a mixed model to account for baseline values of key patient variables.

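### The target-v-sham effect size depends on no carry-over being seen by a test with about 7–20% power, and OFC v SMA is compared by paired tests that ignore period

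*Protocol article*

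**What the plan says.** All statements are in the protocol article.

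- Likely effect size sets the main contrast at 24 h after the last stimulation of each course: "The observed and the lower limit for the effect size for the OFC and SMA targets will be evaluated with respect to the Sham condition". The same sentence attaches the condition "assuming that no carryover effects are observed in the crossover design (mixed model"). A further sentence says that, where possible, "treatment target differences will be adjusted in a mixed model to account for baseline values of key patient variables".
- Sample size calculation gives the basis of the condition: "we assume no carry-over effects, which will be tested using a mixed model". The reasons offered are that each condition has only four exposures and that courses are 4 weeks apart.
- Effect of tDCS says of the two active targets: "Comparison of the OFC and SMA targets will be considered using paired tests to determine if one target is superior to the other". Paired tests are also stated for changes over time ("Time-dependent changes in the Y-BOCS scores, and in the CANTAB test scores will be considered using standard paired comparisons") and for the neurocognitive tests.
- Randomisation scheme uses all six orders of the three conditions, four patients each, which makes 24. Sample size calculation enrols 25 and allows for 5 losses.
- Progression to a full trial lists a lower limit for the effect size above 0.1 among the principal data for the decision.

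**The concern.** A rule that lets an estimate stand if a preliminary test finds nothing is only as good as the test. Carry-over is hard to estimate in a crossover trial of 20 to 25 patients, so the likely result is that none is observed, whether or not it exists. The estimate would then go forward with an assurance that the data cannot give.

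This matters because the lower limit is compared with a fixed figure and the plan's own calculation clears that figure narrowly. A beneficial carry-over that goes unseen pulls the contrast with sham towards zero, so the risk is that a useful target looks too weak to take forward.

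The second part concerns OFC v SMA. A paired test takes no account of when each course was given, so any trend from the first to the third course enters the error. Once the orders are unequally filled, it enters the estimate as well.

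**Working it through.** **1. The plan's lower limit.** Inputs from Sample size calculation: n = 20, expected d = 0.3, and "assuming *α* = 0.05, 1 – *β* = 0.80". Treating d as a within-patient effect with a one-sided 80% limit:

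0.3 − 0.842 × √(1/20) = 0.3 − 0.188 = 0.112.

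This reproduces the stated lower limit above 0.1, with a margin of 0.012. Other readings do not reproduce it: two independent groups of 20 give 0.034, and a one-sided 95% paired limit gives −0.068.

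**2. Power of the carry-over test.** The six orders over three periods were fitted with patient, period, condition and first-order carry-over from the preceding active course. The paired SD is √2 times the within-patient SD, so the noncentrality is L√2/√v, where L is the carry-over in paired-SD units and v is the variance of the carry-over estimate in units of the within-patient variance. The document gives no level for the test, so two-sided 5% is assumed. The 20 completers are taken as 4, 4, 3, 3, 3, 3.

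| Completers | Carry-over terms | v | df | Power, L = 0.15 | Power, L = 0.30 |
|---|---|---|---|---|---|
| 24 | one shared | 0.141 | 43 | 8.6% | 19.8% |
| 24 | one per target | 0.188 | 42 | 7.7% | 16.0% |
| 20 | one shared | 0.160 | 35 | 8.1% | 17.8% |
| 20 | one per target | 0.221 | 34 | 7.2% | 14.2% |

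Example, second row: 0.15 × 1.414/√0.1875 = 0.49, giving 7.7%. At a two-sided 10% level the ranges are 13–15% and 23–30%. Only a full carry-over of a large effect (d = 0.65) reaches 48–67% at the 5% level.

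**3. Effect of a missed carry-over.** In the orders listed under Randomisation scheme, sham follows an active course in C, D, E and F (4 of 6). SMA follows OFC in B and F (2 of 6), and OFC follows SMA in A and C (2 of 6). If either active course leaves a carry-over L and sham leaves none, target v sham shifts by

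(2/6 − 4/6) × L = −L/3.

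- L = 0.15 (half the effect): shift −0.05; lower limit 0.112 − 0.05 = 0.062.
- L = 0.30 (equal to the effect): shift −0.10; lower limit 0.012.
- Carry-over that uses up the margin: 3 × 0.0118 = 0.035, which is about 12% of 0.3.

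This needs no dropout or imbalance.

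**4. Period in OFC v SMA.** The period difference, OFC minus SMA, over orders A to F is +1, −1, +1, +2, −2, −1. The mean is 0 and the variance is 2. With four per order a linear trend therefore gives no bias. With a step of s paired SDs per period it inflates the SD of the paired difference by √(1 + 2s²): 1.010 for s = 0.1 and 1.086 for s = 0.3.

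With 20 completers drawn at random from 25, the mean period difference between two conditions has SD 0.15 and a 95% range of ±0.3 periods. All pairs of conditions are alike in this by symmetry. For s = 0.1 to 0.3 (assumed; the document gives no trend), that range is ±0.03 to ±0.09 SD.

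A concentrated case, with A to F holding 4, 5, 2, 1, 4, 4 patients, gives (4 − 5 + 2 + 2 − 8 − 4)/20 = −0.45 periods, or −0.045 to −0.135 SD.

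**The case against.** The 4-week washout was chosen to avoid carry-over, each course has only four stimulations, and the plan admits limited power elsewhere. Carry-over may well be small. That stands as an argument for the washout, but not for the test. Duration of effect is itself listed as an unknown to be measured, and a carry-over of about 12% of the effect is enough to use up the planned margin.

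An article may leave the full model, and what follows if carry-over is seen, to another document. That stands too, and neither omission is the point here. The condition on the estimate and the paired test for OFC v SMA are both written in the article.

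Four stronger readings are tempting, and the documents do not support them:

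- A reader might infer that target v sham is itself analysed by paired tests. Paired tests are stated for OFC v SMA, change over time and the neurocognitive tests. For target v sham the text names a mixed model and does not list its terms, so a missing period term cannot be claimed there.
- A reader might infer that order effects bias the results. With four per order the bias is exactly zero. Random losses add noise centred on zero, small beside a standard error of about 1/√20 = 0.22. A shift near 0.1 needs both an assumed trend and losses concentrated in particular orders.
- A reader might infer that progression turns on the lower limit alone. It is one of several principal data, weighed with all findings.
- A reader might infer that each course's Day-1 score is left out of the adjustment. The wording on baseline variables does not exclude it.

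**Conclusion.** The concern holds for the carry-over condition. At d = 0.3 the test detects a carry-over half the size of the effect about 7–9% of the time, and one of equal size 14–20% of the time. A missed carry-over of half the effect lowers the planned limit from 0.112 to about 0.062. The direction is towards no effect if the carry-over is beneficial.

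These figures assume first-order carry-over that is the same for both targets and nil for sham, 20 to 24 near-balanced completers, a two-sided 5% test, and the 80% one-sided limit that reproduces the plan's figure. They also read the progression rule as a limit above 0.1, as in Sample size calculation and Progression to a full trial. Likely effect size prints the inequality the other way, which needs correcting separately.

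The point on OFC v SMA is smaller. Ignoring period adds error, and adds a chance shift once the orders are unequal. Its size rests on a period trend that the document does not give.

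**What to change.** Remove the absence of observed carry-over as a condition on the estimate. Fix one mixed model at 24 h, on the outcome named as primary, with condition (sham, OFC, SMA) and period as fixed effects and a random patient effect, using every available course. Take OFC v sham, SMA v sham, OFC v SMA and the lower limits from that model. Keep the paired tests as description only. Adjustment for each course's Day-1 score is optional.

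Report two sensitivity analyses: a carry-over-adjusted estimate, and mean pre-course baselines by previous condition. The adjusted estimate should not be the main one. In the layouts above, adding carry-over terms raises the variance of target v sham by 16–25% (for example 0.104/0.0833 = 1.25 with 24 completers and one term per target).

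The cost is wording only, with no new data. The period term takes 2 degrees of freedom. Its cost in variance is 0% with 24 balanced completers, 0.8% with 20 near-balanced completers, and about 6–7% if all five losses fall on two orders.

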A recent double-blind, randomised, and sham-controlled study investigated the efficacy of tDCS as add-on treatment for treatment-resistant OCD (*n* = 43) [38]. Over 20 consecutive weekdays of active or sham tDCS sessions (30 min, cathode was positioned over the SMA and the anode over the left deltoid) were administered, followed by an 8-week follow-up. Patients that received active tDCS achieved a significant reduction of OCD symptoms than those that received sham at week 12, with mean (*SD*) Yale-Brown Obsessive–Compulsive Scale (Y-BOCS) score changes of 6.68 (5.83) and 2.84 (6.3) points, respectively (Cohen’s *d*: 0.62 (0.06–1.18), *p* = 0.03), with no between-group differences in responders (four patients in the active tDCS and one in the sham group) [38]. There were no significant effects in reducing symptoms of depression or anxiety, and patients in both groups reported mild adverse events [38]. Also based on theoretical and computational models, authors suggest that overall cathodal tDCS may be better than anodal in treating OCD patients with an extracephalic montage [23, 33].

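### Each target–sham effect size is reported on condition that no carry-over is observed, but at the planned size the carry-over test is too weak to support that condition

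*Protocol article*

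**What the plan says.** The Sample size calculation section relies on the small number of exposures and the gap between courses: "with 4 weeks between exposures, we assume no carry-over effects, which will be tested using a mixed model". The Stimulation schedules section gives the washout the same purpose: "Each 2-day course of tDCS will be spaced 4 weeks apart to avoid carry-over effects".

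Under Likely effect size, the main comparison is at 24 h after the last stimulation of each course. Each target's effect size and lower limit against sham are evaluated "assuming that no carryover effects are observed in the crossover design (mixed model". Adjustment for baseline values of key patient variables is foreseen only where possible.

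The Progression to a full trial section lists a lower limit above 0.1 among its principal items. The others are acceptability, recruitment feasibility and the neurocognitive profile.

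**The concern.** The article does more than assume that carry-over is absent. It ties the effect size to a preliminary test not finding any. A non-significant result helps only if the test had a fair chance of detecting a carry-over large enough to matter, and the article gives no power for it.

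The document's own evidence on persistence is mixed. The Background cites a trial with the cathode over the SMA, 20 weekday sessions of 30 min, where "Patients that received active tDCS achieved a significant reduction of OCD symptoms than those that received sham at week 12", that is, eight weeks after the last session. That course was far longer (20 × 30 = 600 min, against 4 × 20 = 80 min here). The Background also cites an OFC trial in which active stimulation was not superior to sham at the 12-week follow-up. Duration of effect is one of the things this study sets out to learn. So neither absence nor presence of carry-over at four weeks can be taken as given.

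At stake is whether the effect size and lower limit that inform progression are sound. A weak test would usually be reported as reassurance whether or not carry-over was present.

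**Working it through.** **Inputs from the article.** Six orders of three courses, four patients per order (Randomisation scheme). 20 completers and "a conservative estimate of *d* = .3 is assumed" (Sample size calculation). "assuming *α* = 0.05, 1 – *β* = 0.80" is stated for the sample size; no level is stated for the carry-over test.

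**Assumptions.** Two-sided 5% carry-over test. First-order carry-over, equal for both targets, of 25%, 50% or 100% of the effect. Patient random effect with within-patient correlation 0.7 (0.5 to 0.8 changes little on the paired scale). Completers spread 4, 4, 3, 3, 3, 3 over the orders.

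**1. Reproduce the plan's own figures.** A two-sided 5% paired t test with N = 20 has power 0.787 at 0.65 (stated .78) and 0.904 at 0.77 (stated .90). The article's effect sizes are therefore on the scale of the SD of paired differences, which is used below.

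The article says that 20 patients "allows detection of a lower limit of *d*’ > 0.1 for an expected effect size" of 0.3. With SE = 1/√20 = 0.224, a one-sided 80% limit is 0.3 − 0.842 × 0.224 = 0.112, which reproduces this claim. A one-sided 95% limit would be −0.068. The slack over 0.1 is thus 0.012.

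**2. Power of the carry-over test.** The model has patient, course number, condition and one term for a preceding active course.
- SE of the carry-over term: 0.394 within-patient SD ÷ √2 = 0.279 paired SD.
- Residual df: 60 − 20 − 2 − 2 − 1 = 35; critical t = 2.03.
- 95% CI half-width: 2.03 × 0.279 = 0.57, almost twice the assumed effect.

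| Carry-over | Size | Size ÷ SE | Power, 1 df | Power, 2 df |
|---|---|---|---|---|
| 25% | 0.075 | 0.27 | 6% | 6% |
| 50% | 0.15 | 0.54 | 8% | 7% |
| 100% | 0.30 | 1.08 | 18% | 14% |

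With 24 completers the 1-df figures are 6%, 9% and 20–21%. Other assumptions give more power. With 20 completers and full carry-over it is about 60% if the true effect is 0.65, 36% if 0.3 is in raw SD units with correlation 0.8, and 27–28% for a 10% test.

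**3. Bias if carry-over is present and scores are not corrected for course baseline.** Sham follows an active course in 4 of the 6 orders. Each active target follows the other in 2 of 6. The active–sham contrast moves by (2/6 − 4/6) × carry-over = −1/3 × carry-over.

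| Carry-over | Effect read | Expected 80% lower limit | Chance limit > 0.1 |
|---|---|---|---|
| none | 0.30 | 0.112 | 52% |
| 25% | 0.275 | 0.087 | 48% |
| 50% | 0.25 | 0.062 | 43% |
| 100% | 0.20 | 0.012 | 35% |

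The expected limit reaches 0.1 when carry-over/3 = 0.0118, that is 0.035, or about 12% of the effect.

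**4. Bias if change from course baseline is used.** Table 1 schedules the Y-BOCS and its challenge version at Day 1 baseline of every course. A stable carry-over is then in both scores and cancels. One that decays between Day 1 and the 24 h assessment reduces the apparent improvement, and does so more often for sham, so the active–sham effect is overstated.

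**5. Cost of adjusting.** Fitting carry-over multiplies the variance of each active–sham contrast by about 1.16 (one common term) to 1.22–1.24 (one term per target). At N = 20 and 0.3 the expected 80% limit becomes 0.3 − 0.188 × √1.16 = 0.097 to 0.3 − 0.188 × √1.24 = 0.090.

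**The case against.** The strongest reply is that carry-over may well be negligible. Each course has four stimulations, the four-week gap was chosen to avoid carry-over, and the OFC trial in the Background showed no lasting superiority. Retaining half or all of a 24 h effect for four weeks is an assumption. Even then, a bias of 0.05 at half carry-over is small beside a paired SE of 0.224. This stands as a limit on the likely harm. It does not make the test informative.

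Several stronger readings are tempting, and the article does not support them.
- A reader might infer that carry-over must shrink the effect. That needs a beneficial carry-over and scores not corrected for course baseline. The article does not say which scores enter the model, and baselines are collected at each course.
- A reader might infer that the test always has under 20% power. That holds at the planning inputs with a 5% level, not at larger true effects, on other scales or at other levels.
- A reader might infer that there is no plan if carry-over is found, or that one test in twenty will be falsely positive. The fallback may sit in the full protocol or analysis plan, and no level is stated for this test.
- A reader might infer that this estimate decides progression. The article weighs all findings, and the effect size is one principal item among several.

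**Conclusion.** The point holds as a fault in a stated analysis rule: an effect size that informs progression should not depend on a preliminary test that cannot do its job. At 20 completers, paired effect 0.3 and an assumed two-sided 5% level, power is about 8% for carry-over of half the effect and 18% for carry-over equal to it. The possible bias is about one third of the carry-over towards zero on uncorrected scores, and may run the other way on change from course baseline. The size of any carry-over is unknown, and the document's evidence on whether four weeks suffices points both ways. The matter is worth correcting because the planned margin over 0.1 is only 0.012 and the correction is cheap. It does not show that the trial's effect estimate will be wrong.

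**What to change.** In Sample size calculation and Likely effect size, delete the condition that no carry-over is observed. Name one primary model in advance, with patient, course number, condition and the course's own Day 1 baseline. Report its estimate and lower limit for each target against sham whatever any carry-over test shows.

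Beside it, as a sensitivity analysis, report the estimate adjusted for first-order carry-over (estimable because all six orders are used) and the carry-over estimate with its 95% CI. State which estimate is compared with the 0.1 limit. When editing, also reconcile the direction of that limit: Likely effect size gives below 0.1 as the positive signal, while Sample size calculation and Progression to a full trial use above 0.1.

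The cost is wording and one extra model. The companion contrasts have about 16–24% more variance, so intervals are about 8–11% wider (√1.16 = 1.08, √1.24 = 1.11). The companion's expected lower limit at N = 20 and 0.3 is about 0.09 to 0.10 in place of 0.112, just under 0.1 even without carry-over. This is why the estimate that counts must be named beforehand.
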